#### Dementia Specific Quality of Life

Because utility based instruments are generic measures, a measure of attributes specific to residents with dementia is also needed [76]. We have selected the caregiver version of the Quality of Life - Alzheimer's Disease (QOL-AD) instrument because it has excellent psychometric properties, is brief (generally administered in 10 minutes), and is based on a sound conceptual framework. The QOL-AD was developed to capture the domains considered important to health-related quality of life in Lawton's broad conceptual framework: the interpersonal; environmental; functional; physical; and, psychological domains [77,78]. The 13 items including physical health, energy, mood, living situation, memory, family, marriage, friends, self as a whole, ability to do chores around the house, fun, money and life as a whole scored on a 4-point Likert scale ranging from 1 (poor) to 4 (excellent). Total scores range from 13 to 52 with 6 points on the QOL-AD scale equivalent to 1 standard deviation. The instrument has demonstrated responsiveness to change [79,80] and good evidence of reliability (coefficient α = 0.87; ICC = 0.92) and validity [80-83]. Caregiver ratings on the QOL-AD were not correlated with various levels of the person with dementia's cognitive functioning. Criterion related validity was demonstrated with Pearson correlation coefficients for measures of behavioural competence, psychological status, physical function and interpersonal environment [82,84]. Some individual item scores for the person with dementia do not correlate with those of the proxy caregiver [82,84].

### Covariates

Depression, cognitive impairment, and comorbidities have been identified as important predictors of loss of mobility [85-87]. Measures for each of these covariates can be derived from the Resident Assessment Instrument 2.0 (RAI 2.0) [88-90] which is completed quarterly in all Alberta LTC facilities. We have opted to use these data for some of the covariate measures to minimize response burden. For each resident participant we will acquire the RAI 2.0 data directly from the LTC facility for the three quarters that best approximate the times in which resident's baseline, three month and six month outcome data are collected. We will use the following scales derived from the RAI 2.0: the *MDS Depression Rating Scale (DRS) *[91,92]; the *Cognitive Performance Scale (CPS) *[93-95]; and, the *Changes in Health, End-stage disease Symptoms & Signs Scale (CHESS) *[96].

The degree to which the environment supports the person with dementia has been identified as an important predictor of loss of mobility [4]; therefore we will use the *Professional Environmental Assessment Protocol *(PEAP) and the *Alberta Context Tool *(ACT) as covariates. The PEAP provides a global assessment of the quality of dementia care environments on nine dimensions deemed to be therapeutic for people with dementia: awareness and orientation, safety and security, provision of privacy, regulation of stimulation, quality of stimulation, support of functional abilities, opportunities for personal control, facilitation of social contact, and continuity of the self with the past through personal and familiar objects. It involves a subjective evaluation of the physical and social environment on a 13-point scale for each dimension, with total scores ranging from 13 to 117 [97]. All PEAP dimensions have demonstrated good inter-rater reliability: percentage agreement from 58.3 to 91.7%, Spearman's from 0.69 to 0.88 and kappas from 0.69 to 0.85 [98]. The PEAP total scores correlate with the more established Therapeutic Environment Screening Scale (r = 0.89) [99] providing evidence for criterion-related validity [100]. Correlations among the PEAP dimensions ranged from 0.45 to 0.85 and a principal components analysis generated a single factor structure for the nine PEAP dimensions accounting for 67% of the total variance [101]. The PEAP summary scores discriminated between special care units and integrated facilities in rural Canadian LTC facilities [101].

The Alberta Context Tool (ACT) which measures organizational context in health care settings was developed to predict research utilization. It consists of eight dimensions that are potentially modifiable: culture, leadership, evaluation, social capital, informal interactions, formal interactions, structural and electronic resources, and organizational slack [102]. The ACT comprises 56 multiple choice items scored on five-point scales with the exception of the structural and electronic resources items scored on a six-point scale. Psychometric properties of the measure were assessed with a sample of health professionals in six Canadian pediatric hospitals [103]. A principal components analysis generated a 13 factor structure accounting for 59% of the total variance. Correlations among the 13 ACT factors ranged from 0.54 to 0.91providing evidence for internal consistency. Instrumental research utilization [103] was correlated with 12 of the 13 ACT factors at the 5% level of significance providing evidence of construct validity.

Facility level characteristics such as size of facility, size of unit and ownership model (public, private for-profit, voluntary not-for-profit) are also potential predictors of resident outcome.

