### Sample Size

The sample size calculation for the number of resident participants is based on the primary outcome measure in the pilot study: the number of sit-to-stands that the resident is able to complete in 30 seconds. Based on our earlier pilot work, we observed residents' ability to maintain and in some instances increase the number of sit-to-stands that they could complete in 30 seconds. We judge an increase of two sit-to-stands completed in 30 seconds to be a meaningful change in the residents' mobility. Based on existing research [10,38,46,47] and the pilot study, the standard deviation of the 30-second sit-to-stand measure is 3.5 sit-to-stands. Thus we will need 49 residents in each of the intervention and the control groups to detect an increase in the number of sit-to-stands that the resident is able to complete in 30 seconds (power = 0.80; 2-tailed; α = 0.05). Assuming an attrition rate of 20% over 6 months we will recruit 60 residents to the intervention group and 60 residents to the control group. We expect to succeed in recruiting and following our sample of 120 residents based on our experience with the pilot study and the experience of [name] who recruited similar samples in two previous studies using similar recruitment methods [4,48].

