### Control group

Resident participants in the control facilities will receive usual care. The only change in their routine will be the measurement of mobility, function and health-related quality of life on three occasions as for residents in the intervention group. Health care aides may work in more than one unit in a facility thus intervention and control groups will be designated at the facility level rather than the unit level to avoid contamination of the control group. It is also possible that some health care aides may work in more than one facility. We will assess the extent of contamination of the control group at the end of the study by asking health care aides who work control facilities if they have ever encouraged residents in the control facilities to repeat sit-to-stands.

LTC facilities in the intervention group will be matched to the control group facilities on ownership model (public, private for-profit, voluntary not-for-profit) and size because quality of care and resident outcomes are associated with ownership models [49-54] and size [48,49,52]. To assess the comparability of the intervention and control facilities a research assistant will gather information about each facility by: a) interviewing managers to obtain information such as staff-to-resident ratios on each shift, availability of rehabilitation services and size of units; b) observing activity across both the day and evening shifts using a structured observation schedule; and c) measuring environments using two standardized instruments: the Alberta Context Tool and the Professional Environmental Assessment Protocol (PEAP). Drawing on data collected from the observations and data elicited during the manager interviews, total PEAP scores will be calculated immediately following each manager interview.

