### Schedule of Intervention

After obtaining informed consent the research assistant will gather residents' demographic information and measure residents' baseline mobility, function, and health-related quality of life in both the intervention and control groups (see Figure 1). The extent of baseline measurement is limited because of the frailty of this population and the likelihood of attrition during the study period. After baseline measurement the mobility intervention will be introduced exclusively to residents in the intervention group. Resident outcomes will be measured for both the intervention and comparison groups at three months and six months.

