### Procedure

As the first residents are recruited from each intervention facility we will introduce the sit-to-stand intervention to the intervention facilities on the units where the residents reside. A nurse educator contracted for the study will deliver 20 minute education sessions on the sit-to-stand functional activity to as many health care aides as possible who are working on both day and evening shifts. These 20 minute sessions will be offered between 8 and 32 times depending on the size of the intervention facility. During these small group education sessions we will: a) describe the potential rationale for the sit-to-stand activity; b) provide standardized instruction and practice of the activity; and, c) illustrate how to document resident participation with the sit-to-stand activity. Following the education sessions health care aides will begin to facilitate the sit-to-stand activity with residents in their care who have been recruited to the study. Our pilot study demonstrated that health care aides require encouragement at regular intervals to consistently integrate the sit-to-stand activity into their daily routine. Thus we have included knowledge translation interventions that were tested in the pilot study to optimize the likelihood that residents in the treatment group will perform the sit-to-stand activity. In the first month the nurse educator will return to the intervention facilities to converse with the health care aides about their experiences with the sit-to-stand activity and to facilitate problem-solving around any barriers that they may have encountered. In the second month a set of reminders will be introduced including: a) prominently posting the names of resident participants where the change of shift occurs; b) affixing a colourful sticker to residents' bedroom doors and beside their beds; and, c) marking with a sticker the usual documentation flowsheets where the health care aides record residents' shift-to-shift responses to the exercise. During the third month 20 minute problem solving sessions with health care aides will be conducted to identify barriers to completing the sit-to-stand activity and to suggest ways to overcome them. The next month a poster and small handouts that summarize the discussion and problem-solving sessions will be posted on the treatment units and distributed to the health care aides. Each month a different approach will be taken to heighten the awareness of the health care aides about the importance of continuing to integrate the sit-to-stand activity into the residents' activities of daily living.

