### Data Analysis

All data will be entered into an SPSS 19 database (IBM, 2010, ^©^IBM Corporation). Ten percent of the data will be double entered to assess the accuracy of data entry. We will compare the baseline characteristics of the LTC facilities, health care aides, and residents in the intervention group with the control group by computing descriptive statistics. Data are structured for each outcome measure (the 30-second sit-to-stand test; the *Functional Independence Measure*; the *Health Utilities Index Mark 2 and 3; *and, the *Quality of Life - Alzheimer's Disease*) to allow a mixed between-within subjects analysis of covariance. Specifically, the between subjects factor consists of the two groups (Control versus Intervention Group) and the within subject factor consists of the repeated measures. The covariates will include baseline characteristics the residents, including age, sex, level of cognitive impairment (Cognitive Performance Scale), extent of depression (MDS Depression Rating Scale), and extent of health instability (CHESS), and characteristics of the LTC facilities including facility size, unit size, ownership model, and quality of the environment (PEAP and ACT). A Multivariate Analysis of Covariance (MANCOVA) will be used to control the experiment-wise error rate for comparisons. Data will be analyzed according to the intention-to-treat principle, i.e. residents who relocate to another setting or who die before completing the six months of follow-up will be included in the data analysis. The extent to which the residents in the intervention facilities actually received the mobility interventions will be assessed using the documentation flowsheet measures to establish a graphical analysis of the covariate-corrected time course of performance on the mobility intervention. These analyses will be conducted using SPSS 19 in consultation with a statistician from the Centre of Health Promotion Studies at the University of Alberta.

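### The rule for choosing the baseline RAI 2.0 record lets it post-date baseline, so some intervention residents could be adjusted for depression, cognition and health-instability scores recorded after exposure began

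*Protocol article*

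**What the plan says.** Under Covariates, the Cognitive Performance Scale (CPS), the MDS Depression Rating Scale (DRS) and CHESS are derived from the RAI 2.0, "which is completed quarterly in all Alberta LTC facilities". The records are obtained from the facility "for the three quarters that best approximate the times in which resident's baseline, three month and six month outcome data are collected". This is a closeness criterion. It does not say on which side of the baseline date the first record must lie.

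Data Analysis then gives these scores the status of pre-treatment covariates: "The covariates will include baseline characteristics the residents, including age, sex, level of cognitive impairment (Cognitive Performance Scale), extent of depression (MDS Depression Rating Scale", with CHESS listed next.

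On timing, Schedule of Intervention states: "After baseline measurement the mobility intervention will be introduced exclusively to residents in the intervention group". Procedure adds: "Following the education sessions health care aides will begin to facilitate the sit-to-stand activity with residents in their care who have been recruited". The number of days from baseline to first exposure is not given. Under Control group, "Resident participants in the control facilities will receive usual care".

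**The concern.** A covariate used to adjust a group comparison should be fixed before treatment can touch it. The selection rule under Covariates does not secure that, although Data Analysis relies on it. With quarterly records, the closest one may lie after baseline, and in an intervention facility it may then lie after aides have begun the activity.

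Three features of this study make the point worth raising:

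- **No randomisation.** Six matched facilities are compared, so resident-level adjustment carries much of the confounding control. The Covariates section itself presents mood, cognition and comorbidity as predictors of mobility loss.
- **Overlap with the outcomes.** The HUI2/3 scores emotion and cognition, the QOL-AD includes mood and memory, and the FIM has a cognitive subscale. A DRS or CPS score recorded under exposure could absorb part of the effect being estimated.
- **Source of the score.** The RAI 2.0 is the facility's own record, and staff in intervention facilities know the intervention is running. Any change in rating would occur in one arm only.

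**Working it through.** **The plan's own figure.** The document gives no figure for RAI timing. Its one design calculation is the sample size: 2 × (1.96 + 0.842)² × 3.5² / 2² = 48.1, rounded up to 49 per group, which reproduces the stated 49. Sample Size then says: "we will recruit 60 residents to the intervention group and 60 residents to the control group". Only the 60 per group is used below.

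**Inputs.**
- RAI interval: quarterly (Covariates). Q = 365.25 / 4 = 91.3 days.
- Exposed residents: the 60 in the intervention group only (Schedule of Intervention; Control group).
- Lag L from baseline to first exposure: not stated, so taken as 0 to 30 days (assumption).
- Baseline date: uniform within the RAI cycle, with the closest record taken (assumption).

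**Share recorded after the baseline date.** The closest record lies between Q/2 before and Q/2 after baseline. Half of the records fall after it, on average Q/4 = 22.8 days later and at most Q/2 = 45.7 days later.

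**Share recorded after exposure began.** For intervention residents the share is (Q/2 − L) / Q. The mean exposure among those affected is (Q/2 − L) / 2.

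| Lag L (days) | Share of intervention group | Residents of 60 | Share of all 120 | Mean days exposed before the record |
|---|---|---|---|---|
| 0 | 45.7/91.3 = 50% | 30 | 25% | 22.8 |
| 7 | 38.7/91.3 = 42% | 25 | 21% | 19.3 |
| 14 | 31.7/91.3 = 35% | 21 | 17% | 15.8 |
| 30 | 15.7/91.3 = 17% | 10 | 9% | 7.8 |

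A simulation of one million draws gave the same shares.

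**Which lag is plausible.** Procedure brings the activity to a unit as its first residents are recruited, while Sampling and recruitment expects most enrolment to take eight months. Later recruits can therefore join units whose aides are already trained, which points to short lags for them. The first recruits wait for the education sessions. The document does not settle where in the range the study would fall.

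**Under a last-record-on-or-before-baseline rule.** No record can follow exposure. The age of the record is uniform from 0 to Q, with mean Q/2 = 45.7 days and maximum 91.3 days. Under the closest-record rule the mean distance is 22.8 days and the maximum 45.7.

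**The case against.** The strongest reply has three parts.

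**The article is condensed.** It gives no date window, and calling the scores baseline characteristics is compatible with picking a pre-intervention record. A full protocol might say so. That is fair as to the exact window. But the article does state a selection rule, and that rule, as worded, admits records from after baseline. The two sections do not guarantee the same thing.

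**The closest record may describe baseline best.** In a frail population an older CHESS or DRS score measures baseline status less well. This stands as a real cost. It falls on both arms alike, however, whereas contamination by treatment falls on one.

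**The effect is likely negligible.** Nothing in the document shows that this activity shifts mood, cognition or health stability within a few weeks. Suppose, purely for illustration, that exposure moves a covariate by 0.2 SD and that 1 SD is worth 1 stand. The adjusted effect then moves by 0.50 × 0.2 × 1 = 0.10 stand at zero lag, or 0.17 × 0.2 × 1 = 0.03 stand at a 30-day lag. The unadjusted standard error of the difference with 49 per group is 3.5 × √(2/49) = 0.71 stand, so the larger shift is about 0.14 standard errors. Neither assumed input is in the document, so this shows scale only. It does support treating the point as minor for the 30-second test.

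Two stronger readings are tempting and fail:

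- A reader might infer that about half of all residents have covariates recorded under exposure. Half is the share recorded after the baseline date. Controls are never exposed, so the ceiling under uniform timing is half of one arm.
- A reader might infer from the acquisition of 3- and 6-month RAI scores that these too will be adjusted for. Data Analysis names only baseline resident characteristics, and no section enters the later scores in the group comparison.

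**Conclusion.** The point holds as a cheap improvement. The article pairs a closest-quarter rule with adjustment for scores treated as baseline, in a design where exposure follows baseline in one arm only. Under uniform RAI timing and a lag of 0 to 30 days, about 30 down to 10 of the 60 intervention residents (25% to 9% of all 120) would carry a covariate recorded after exposure began. Both conditions are assumptions. If baseline visits were arranged around RAI dates, the share could be higher or lower.

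A reader might go on to infer a material bias in the treatment effect. The document does not support that. The record follows baseline by at most about 46 days, and no figure is given for the activity's effect on these scales or for their relation to the outcomes. The bias is probably small. Overlap with the quality-of-life measures gives more reason for care there, but its size cannot be worked out from the document either.

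**What to change.** In Covariates, define the baseline CPS, DRS and CHESS as those from the most recent RAI 2.0 completed on or before the resident's own baseline measurement. Report the interval from RAI to baseline by group, so that readers can see how old the scores are and whether the arms differ.

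The anchor should be the resident's own baseline date, not aide training on the unit. With recruitment spread over eight months or more, a training-date condition could force very old records, or leave none for residents admitted later.

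The cost is one sentence and a different extraction date in data the facilities already produce. The downside is staleness: a mean record age of about 46 days (maximum about 91), against a mean distance of about 23 days (maximum about 46) under the present rule.

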### Data Analysis

All data will be entered into an SPSS 19 database (IBM, 2010, ^©^IBM Corporation). Ten percent of the data will be double entered to assess the accuracy of data entry. We will compare the baseline characteristics of the LTC facilities, health care aides, and residents in the intervention group with the control group by computing descriptive statistics. Data are structured for each outcome measure (the 30-second sit-to-stand test; the *Functional Independence Measure*; the *Health Utilities Index Mark 2 and 3; *and, the *Quality of Life - Alzheimer's Disease*) to allow a mixed between-within subjects analysis of covariance. Specifically, the between subjects factor consists of the two groups (Control versus Intervention Group) and the within subject factor consists of the repeated measures. The covariates will include baseline characteristics the residents, including age, sex, level of cognitive impairment (Cognitive Performance Scale), extent of depression (MDS Depression Rating Scale), and extent of health instability (CHESS), and characteristics of the LTC facilities including facility size, unit size, ownership model, and quality of the environment (PEAP and ACT). A Multivariate Analysis of Covariance (MANCOVA) will be used to control the experiment-wise error rate for comparisons. Data will be analyzed according to the intention-to-treat principle, i.e. residents who relocate to another setting or who die before completing the six months of follow-up will be included in the data analysis. The extent to which the residents in the intervention facilities actually received the mobility interventions will be assessed using the documentation flowsheet measures to establish a graphical analysis of the covariate-corrected time course of performance on the mobility intervention. These analyses will be conducted using SPSS 19 in consultation with a statistician from the Centre of Health Promotion Studies at the University of Alberta.

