**Methods/Design:**

This longitudinal, quasi-experimental study is designed to demonstrate the effect of the sit-to-stand activity carried out by residents in the context of daily care with health care aides. In three intervention facilities health care aides will prompt residents to repeat the sit-to-stand action on two separate occasions during each day and each evening shift as part of daily care routines. In three control facilities residents will receive usual care. Intervention and control facilities are matched on the ownership model (public, private for-profit, voluntary not-for-profit) and facility size. The dose of the mobility intervention is assessed through the use of daily documentation flowsheets in the health record. Resident outcome measures include: 1) the 30-second sit-to-stand test; 2) the *Functional Independence Measure*; 3) the *Health Utilities Index Mark 2 and 3; *and, 4) the *Quality of Life - Alzheimer's Disease*.

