### Sampling and recruitment

Residents with dementia residing in six LTC facilities in Edmonton, and the health care aides working with them, will be recruited to participate in the study. The purposive sample of research participants will be recruited from units which serve cognitively and physically frail older adults rather than units for young disabled people or sub-acute units. Residents that have a diagnosis of dementia and are able to transfer independently, or with the assistance of one person, will be eligible for inclusion in the study. Residents with a serious physical illness or life expectancy less than six months at the time of recruitment will be excluded from the study. We expect that most of the resident participants will be recruited to the study within eight months, however recruitment will continue throughout the study if necessary.

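### Treatment is assigned to six facilities, but the stated analysis tests the group effect against resident-level error, so p-values and intervals are too optimistic if facilities vary in the tested contrast

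*Protocol article*

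**What the plan says.** The sample is drawn from a small number of sites: "Residents with dementia residing in six LTC facilities in Edmonton". The abstract gives the split: "In three intervention facilities health care aides will prompt residents" and "In three control facilities residents will receive usual care". The Control group section states the unit of assignment: "intervention and control groups will be designated at the facility level rather than the unit level to avoid contamination of the control group". The same section matches facilities on ownership model and size, on the ground that "quality of care and resident outcomes are associated with ownership models", and says the same of size.

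The Data Analysis section structures the data for each outcome "to allow a mixed between-within subjects analysis of covariance", and then specifies that "the between subjects factor consists of the two groups (Control versus Intervention Group) and the within subject factor consists of the repeated measures". Covariates are resident characteristics (age, sex, cognitive impairment, depression, health instability) and "characteristics of the LTC facilities including facility size, unit size, ownership model, and quality of the environment (PEAP and ACT"). A MANCOVA is added to control the experiment-wise error rate. The section contains no random or nested facility effect, no cluster-robust error and no facility-level degrees of freedom.

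**The concern.** When whole facilities are assigned, chance differences between facilities fall entirely on the group comparison. Residents of one facility share aides, routines, environment and, in the intervention group, the same education and reminders. The article itself treats facility characteristics as predictors of resident outcome. In a between-within analysis whose only between-subjects factor is group, the error term is variation between residents within group, as if each resident had been assigned separately. The comparison really rests on three facilities against three.

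At stake is the error rate for every outcome. A significant result could reflect nothing more than three facilities having drifted differently from three others. The MANCOVA rests on the same error structure and does not help.

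**Working it through.** **Inputs from the article (Sample Size section):** difference 2 sit-to-stands, SD 3.5, power 0.80, two-sided alpha 0.05, 49 evaluable and 60 recruited residents per group. Three facilities per group come from the abstract. **Assumed:** equal facility sizes, ICC from 0.01 to 0.10, and 3.5 as the SD of the quantity analysed, as the article's own calculation does.

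**1. Reproduce the stated sample size.** n = 2 × (1.960 + 0.842)² × 3.5² / 2² = 48.1, so 49 per group, as stated. This formula is for independent residents and contains no design effect, so it matches the error structure in the Data Analysis section.

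**2. Effect of leaving facility out of the error term.** Completers per facility: m = 49/3 = 16.3. Design effect: DE = 1 + (m − 1) × ICC. True type I error of a nominal 5% resident-level test: 2 × [1 − Φ(1.96/√DE)].

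**3. Interval and power with facility as the unit.** Resident-level half-width: 1.96 × 3.5 × √(2/49) = 1.39. Facility-level half-width: t(4 df) × 3.5 × √(2 × DE/49), with t = 2.776. Power for a difference of 2 is from the noncentral t distribution with 6 − 2 = 4 df.

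| ICC (assumed) | DE | True type I error of planned test | 95% half-width, planned | 95% half-width, 4 df | Power, 4 df |
|---|---|---|---|---|---|
| 0 | 1.00 | 5.0% | 1.39 | 1.96 | 57% |
| 0.01 | 1.15 | 6.8% | 1.39 | 2.11 | 52% |
| 0.02 | 1.31 | 8.6% | 1.39 | 2.24 | 47% |
| 0.05 | 1.77 | 14.0% | 1.39 | 2.61 | 37% |
| 0.10 | 2.53 | 21.8% | 1.39 | 3.12 | 28% |

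**4. Do facility covariates repair this?** A resident-level ANCOVA was simulated with one facility covariate plus two ownership dummies (16 residents per facility, 4,000 runs per case; covariates unrelated to the remaining facility variation). Type I error was 8.3%, 14.1% and 23.6% at ICC 0.02, 0.05 and 0.10. Without covariates it was 8.2%, 13.7% and 21.4%. The inflation remains.

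**5. Does testing group-by-time repair this?** A resident-level test of change was simulated with 3 versus 3 facilities of 16 residents. With stable facility differences (intercept ICC 0.10) and no facility variation in change, type I error was 0.048. With an ICC of change of 0.02, 0.05 and 0.10 it was about 0.09, 0.15 and 0.22. The table therefore applies to group-by-time when its ICC column is read as the ICC of change.

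**6. Can the listed covariates be fitted?** If each is measured once per facility, the facility-level columns are intercept (1), group (1), facility size (1), ownership (2), PEAP (1) and ACT (1): 7 columns for 6 facilities. The rank is 6 with group and 6 without it, so the other columns already account for group.

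**The case against.** **Facilities are not ignored.** A reader might infer from the missing facility factor that the plan disregards facilities altogether. The text does not support that: it adjusts for five facility or unit characteristics and matches on two of them. These steps can reduce variation between facilities. They do not model what remains or change the error term, as step 4 shows.

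**Stable differences cancel.** A reader might also infer that any difference between facilities could be declared an intervention effect. That is too strong. The design includes a baseline, and the Intervention group section speaks of the effect over time, so the natural test is group-by-time, where constant facility differences drop out (step 5). This part of the objection stands and limits the claim to facility variation in change. Nothing in the article shows that variation to be zero, and care delivered by shared staff plausibly acts on change.

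**Four degrees of freedom are not the only choice.** Facilities are matched, and an analysis that keeps the three pairs has 2 df (t = 4.30 instead of 2.78). Either is defensible if stated.

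**The covariate problem is conditional.** Unit size may vary within a facility, and PEAP and ACT might if scored by unit; the article does not settle this. Non-estimability follows only if all are measured once per facility.

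**This belongs in an analysis plan.** Detail could. But the article names the factors of the model, and that statement is at odds with its own unit of assignment.

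**Conclusion.** The point holds in this form: assignment is by facility, three against three, and the stated model leaves residual within-facility correlation out of the error term. The direction is certain for any positive ICC of the tested contrast. The size is not known, because the article gives no ICC. Over an assumed range of 0.01 to 0.10, with about 16 completers per facility, true type I error runs from about 7% to 22% against a nominal 5% (a level stated only under Sample Size). At ICC 0.05 an honest 95% half-width is about 2.6 sit-to-stands instead of 1.4, wider than the difference of 2 that the trial is sized to detect.

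Separately, if every listed facility covariate is measured once per facility, the overall group effect cannot be estimated.

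It should not be inferred that a corrected error term would make a positive result fully trustworthy. Assignment is not random, and confounding between the two sets of facilities would remain.

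**What to change.** In the Data Analysis section, analyse change or baseline-adjusted outcomes with facility in the error structure, by one of two routes:

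- a linear mixed model with random facility and facility-by-time effects, residents nested within facility, and small-sample degrees of freedom. A random facility intercept alone is not enough, because it does not enter the group-by-time contrast;
- a two-stage analysis that adjusts for resident covariates and then compares the three and three facility mean changes, on 4 df, or 2 df if the matched pairs are kept. State which in advance.

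Drop facility-level covariates from the primary model, or cut them to what six facilities can support. Each one retained takes from the 4 df. Report the ICC and the facility-level results.

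**Cost.** No new data are needed. Intervals widen, for example from about ±1.4 to ±2.6 sit-to-stands at ICC 0.05 with 4 df. The 80% power in the Sample Size section must be restated: with 4 df and SD 3.5 it is about 57% at ICC 0, 52% at 0.01, 37% at 0.05 and 28% at 0.10. The report should also say that the corrected analysis does not remove confounding from non-random assignment.
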